## Abstract

**Introduction:**

Increased dosing of rifampicin and pyrazinamide seems a viable strategy to shorten treatment and prevent relapse of drug-susceptible tuberculosis (TB), but safety and efficacy remains to be confirmed. This clinical trial aims to explore safety and pharmacokinetics-pharmacodynamics of a high-dose pyrazinamide-rifampicin regimen.

**Methods and analysis:**

Adult patients with pulmonary TB admitted to six hospitals in Sweden and subjected to receive first-line treatment are included. Patients are randomised (1:3) to either 6-month standardised TB treatment or a 4-month regimen based on high-dose pyrazinamide (40 mg/kg) and rifampicin (35 mg/kg) along with standard doses of isoniazid and ethambutol. Plasma samples for measurement of drug exposure determined by liquid chromatography tandem-mass spectrometry are obtained at 0, 1, 2, 4, 6, 8, 12 and 24 hours, at day 1 and 14. Maximal drug concentration (C_max_) and area under the concentration-time curve (AUC_0-24h_) are estimated by non-compartmental analysis. Conditions for early model-informed precision dosing of high-dose pyrazinamide-rifampicin are pharmacometrically explored. Adverse drug effects are monitored throughout the study and graded according to Common Terminology Criteria for Adverse Events V.5.0. Early bactericidal activity is assessed by time to positivity in BACTEC MGIT 960 of induced sputum collected at day 0, 5, 8, 15 and week 8. Minimum inhibitory concentrations of first-line drugs are determined using broth microdilution. Disease severity is assessed with X-ray grading and a validated clinical scoring tool (TBscore II). Clinical outcome is registered according to WHO definitions (2020) in addition to occurrence of relapse after end of treatment. Primary endpoint is pyrazinamide AUC_0-24h_ and main secondary endpoint is safety.

**Ethics and dissemination:**

The study is approved by the Swedish Ethical Review Authority and the Swedish Medical Products Agency. Informed written consent is collected before study enrolment. The study results will be submitted to a peer-reviewed journal.

**Trial registration number:**

NCT04694586.

Strengths and limitations of this studyThis phase II clinical trial of patients with drug-susceptible pulmonary tuberculosis (TB) will provide data on safety and early bactericidal activity in relation to drug exposure of an experimental shorter TB regimen based on high-dose pyrazinamide and rifampicin.The patients’ drug exposure will be related to individual *Mycobacterium tuberculosis* minimal inhibitory concentrations, exploring pharmacokinetics-pharmacodynamics indices during high-dose pyrazinamide and rifampicin.Opportunities for early model-informed precision dosing after the first dose will be explored by pharmacokinetic modelling.A limitation of the study is the small sample size, due to an extensive and resource demanding study protocol, although this is in accordance with phase II studies and will partly be compensated for by using rich data.

## Introduction

Current treatment of drug-susceptible tuberculosis (TB) is based on recommendations by the WHO and originates from the 1970s.^1 2^ During the first 2 months (intensive phase) daily doses of isoniazid 5 mg/kg, rifampicin 10 mg/kg, pyrazinamide 25 mg/kg, and ethambutol 15 mg/kg are given, followed by a continuation phase of isoniazid and rifampicin.^1^ This 6-month multidrug regimen is intended to prevent acquired drug resistance, therapy failure and relapse.^3^ Although effective, the long treatment duration increases the risk of non-compliance. Hence shorter and more effective regimens with preserved safety profile are needed as part of the global strategy to eliminate TB. Several attempts to shorten TB treatment below 6 months have been unsuccessful due to increased frequency of relapse.^4–7^ However, a pooled analysis of patient-level data from 4-month fluoroquinolone-containing regimens identified non-inferiority compared with standard treatment in participants with minimal non-cavitary disease.^8^ Recently, a 4-month rifapentine-based regimen containing moxifloxacin for treatment of pulmonary TB was non-inferior to standard 6-month TB regimen in terms of TB disease-free survival 12 months after randomisation.^9^

Accumulating data from clinical trials exploring higher doses of rifampicin^10–13^ have shown increased bactericidal activity with potential to shorten TB treatment corroborated by results from pharmacokinetic-pharmacodynamic (PK-PD) modelling and simulation.^14 15^ Lately, pyrazinamide has attained increasing attention due to its potent sterilising activity with the ability to eliminate intracellular resting and slowly replicating *Mycobacterium tuberculosis* (*Mtb*) so-called ‘persisters’.^16^ Once the drug was added to standard TB treatment in the early 1980s the treatment length could be shortened from 9 to 6 months without increase in relapse.^2 17^ Efforts to further shorten TB treatment from 6 to 4 months by simply prolonging the duration of pyrazinamide was unsuccessful because of increased frequency of relapse.^18^ Observational studies of more than 100 patients with pulmonary TB^19 20^ and a recent meta-analysis^21^ have shown that unsuccessful treatment outcome was associated with suboptimal pyrazinamide exposure. PK studies in patients with pulmonary TB have shown lower than recommended drug concentration levels^22^ with standard dosing of both rifampicin (42%–80%) and pyrazinamide (27%–53%).^23 24^ In a large PK-PD study evaluating patient-level data from three phase II clinical trials with pulmonary TB patients where the majority had cavitary disease, participants received rifampicin (range 10–35 mg/kg), pyrazinamide (range 20–30 mg/kg) and two companion drugs.^25^ The results showed that pyrazinamide’s induction of culture negativity increased with augmented drug exposure. Hepatotoxicity was rare and not associated with pyrazinamide exposure. Furthermore, PK modelling suggested that a massive dose of pyrazinamide (>4500 mg) or increasing both pyrazinamide and rifampicin doses would be required to reach microbiological targets associated with treatment-shortening such as 90%–95% culture conversion rate by 2 months of treatment.^25^ Rifampicin doses of at least three times the standard dose combined with isoniazid, pyrazinamide and ethambutol was safely administered to 63 patients with pulmonary TB for 12 weeks.^11^ Rifampicin 40 mg/kg was recently identified as the highest tolerated dose with dose limiting factors reported as gastrointestinal disorders, pruritus, hyperbilirubinaemia and jaundice.^26^ However, the safety of simultaneously administered high-dose pyrazinamide and rifampicin remains to be explored. Our study aims to investigate PK-PD data, safety and tolerability of a 4-month first-line treatment with combined high dosing of pyrazinamide and rifampicin to a selected group of patients with non-advanced pulmonary TB.

## Methods and analysis

### Study design

We are conducting a multicentre open-label randomised controlled phase II study. The study protocol conforms with Standard Protocol Items: Recommendations for Interventional Trials, an international format for interventional trials.^27 28^

### Study setting

The study is carried out at infectious disease departments in six hospitals in Sweden, three tertiary level hospitals and three secondary level hospitals. The number of hospital beds in the hospitals range from 310 to 1340. The incidence of TB in Sweden is 4.75/100 000 (2019) and the vast majority (85%) of patients are migrants that have acquired their infection prior to arriving to Sweden.^29^ The number of new culture positive pulmonary TB cases during 2019 was 93 in total within the regions served by the six hospitals included in the study.^29^ A majority of the study participants will be admitted to a hospital ward as per standard of care for isolation of patients with smear positive pulmonary TB. Participants not considered in need of hospital admission or isolation will be followed by frequent outpatient visits as well as hospital admission on day 1 and 14 to facilitate the frequent PK-sampling.

### Study participants

A total number of 40 evaluable patients will be included. Study inclusion and exclusion criteria are listed in table 1.

**Table 1 T1:** Inclusion and exclusion criteria in HighShort-RP

Inclusion criteria	Exclusion criteria
Adult (≥18 years)	Treated for TB within the last year.
Pulmonary TB confirmed by PCR and/or culture for *Mtb*	Molecular or phenotypic resistance to any of the first-line oral drugs
Eligible for first-line TB treatment, but not yet started treatment	Miliary TB or advanced pulmonary TB with sputum smear grade three or advanced TB on chest X-ray according to National Tuberculosis Association (1961)^30^ defined by one or more of the following radiological findings: Cavitation of >4 cm diameter. Disseminated lesions of slight to moderate density which extend throughout the total volume of more than one lung (uni- or bilateral). Radiological signs of dense and/or confluent lesions affecting >1/3 of one lung or in both lungs combined
Hiv-negative	Any other infectious disease of such significance that urgent treatment is required
BMI >17	Ongoing treatment with other medication where treatment with rifampicin can interact with the medication and compensatory drug adjustments cannot be made
Written informed consent to participate in the study	Previously known allergy to any of the first-line drugs or other contraindications according to the Summary of Product Characteristics of rifampicin, isoniazid, pyrazinamide and ethambutol
Fertile women must agree to use a barrier contraceptive during the study and have a negative pregnancy test on inclusion	Immunocompromised defined as primary or secondary immunodeficiency including immunosuppressive treatment such as chemotherapy, immunomodulating agents, corticosteroids equivalent to ≥15 mg prednisolone
	Known liver disease or aspartate aminotransferase or alanine aminotransferase >1.5 times the upper normal level
	Heart failure (NYHA class III and IV)
	Kidney failure (eGFR <50 mL/min)
	Dysregulated diabetes mellitus
	Alcohol or drug abuse
	Pregnancy or breast feeding
	Bodyweight <35 or >90 kg

BMI, body mass index; eGFR, estimated glomerular filtration rate; *Mtb*, *Mycobacterium tuberculosis*; NYHA, New York Heart Association; TB, tuberculosis.

### Study outline

The overall study outline is shown in figure 1.

**Figure 1 F1:**
[figure not shown]
The study outline in the flow chart arrow reflects study activity identical for the intervention and control group. After 4 months treatment, the intervention group is followed up according to the follow-up information found in the bottom of the flow chart arrow, meanwhile the control group is followed up according to routine care (not included in the picture). Study participants are provided with a drug diary to record concomitant drugs, food intake and potential side effects during the treatment. Sputum samples are collected regularly during the study to assess time to positivity in BACTEC MGIT 960 for mycobacterial liquid culture. Rich blood sampling for measurement of drug concentrations is collected on the day of the first dose and after 14 days of treatment. Changes in clinical status is assessed by a clinical scoring tool (TBscore II) in addition to evaluation by chest X-ray and/or thoracic CT. Safety data are monitored closely during the first four study months and is based on urgently reported serious adverse events (AEs), AE questionnaire, medical records, regularly surveillance of blood chemistry and during the first 2 weeks analysis of ECG. The final treatment outcome, according to WHO definitions and occurrence of relapse, is registered for both study arms after treatment completion. TB, tuberculosis.

After providing informed consent patients are screened for eligibility to participate in the study based on the inclusion and exclusion criteria (table 1). A review and registration of the patient’s clinical status and symptoms is made, and any pre-existing symptoms and findings are recorded for future reference as potential adverse event (AE) from high-dose pyrazinamide and rifampicin can overlap with the symptoms of active TB. Provided all the inclusion criteria and none of the exclusion criteria are fulfilled according to the responsible physician, the study participant is electronically randomised in a 1:3 ratio to either open-label standard first-line TB treatment for 6 months or to a shortened treatment of 4 months in the intervention group. The higher doses utilised in the intervention group are 40 mg/kg of pyrazinamide (for 8 weeks) and 35 mg/kg of rifampicin (for 4 months) and with standard dosing of isoniazid (5 mg/kg for 4 months) and ethambutol (15–20 mg/kg for 8 weeks) (table 2). Dose adjustment based on changes in body weight will be evaluated after 2 weeks of therapy.

**Table 2 T2:** Treatment in control and intervention group

Drug	Control group	Intervention group
Pyrazinamide	20–30 mg/kg/day for 8 weeks	40 mg/kg/day for 8 weeks
Rifampicin	10 mg/kg/day for 6 months	35 mg/kg/day for 4 months
Isoniazid	5 mg/kg/day for 6 months	5 mg/kg/day for 4 months
Ethambutol	15–20 mg/kg/day for 8 weeks	15–20 mg/kg/day for 8 weeks

Approved fixed dose combination tablets will be used during the treatment period and in the intervention group combined with single tablets of pyrazinamide and rifampicin to reach target doses of pyrazinamide 40 mg/kg (range 36–43 mg/kg) and rifampicin 35 mg/kg (33–37 mg/kg) according to weight-based tables included in the study protocol.

Clinical evaluation of the participants and disease severity is assessed and documented according to TBscore II (table 3) as well as with chest X-ray.^30 31^

**Table 3 T3:** Parameters used for the TBscore II^31^

Parameters	Points assigned
Self-reported	
Cough	1
Dyspnoea	1
Chest pain	1
Anaemia (pale conjunctiva)	1
BMI (body mass index) <18	1
BMI <16	1
MUAC (middle upper arm circumference)<220 mm	1
MUAC <200 mm	1

TB, tuberculosis.

First-line drug concentration measurements in plasma are determined at 0, 1, 2, 4, 6, 8, 12 and 24 hours after drug intake on day 1 and day 14. Maximal drug concentration (C_max_) and area under the concentration-time curve (AUC_0-24h_) are assessed by non-compartmental analysis using the linear trapezoidal method.^32^ The potential for early model-informed precision dosing of high-dose pyrazinamide and rifampicin will be explored by applying PK modelling on drug concentrations obtained after the first dose vs after 14 days of treatment. Induced sputum samples are collected on day 0, 5, 8, 15 and week 8.

### Collection of safety measures and follow-up

All study participants are monitored throughout the study as per routine care. Additional study-specific visits and monitoring by ECG, blood sampling, sputum collection and radiology is outlined in figure 1. Participants in the study will be provided with a diary to record drug intake and to note any suspected side effects from the treatment. Safety data are collected during the intensive phase by weekly AE questionnaire interviews and from the patient diary, the medical record and by frequent laboratory monitoring for blood chemistry tests as displayed in figure 1. During the continuation phase the same safety routine is applied every second week. AEs are graded based on Common Terminology Criteria for Adverse Events V.5.0. A serious AE (SAE) needs to be reported within 24 hours after the study team has been notified and is defined as death of any cause, life-threatening AE and AE that results in prolonged or new hospital admission or permanent disability. For safety reasons, AE considered to be related to TB treatment and causes cessation of pyrazinamide and/or rifampicin, needs to be reported in the same manner as SAE. Based on these reports a decision is made if the SAE requires any further action in terms of trial continuation. Any new concomitant medication is recorded and evaluated to check for potential interactions with the TB treatment. As an additional safety measure, sputum samples collected during the intensive phase will be used to evaluate the effect of combined high-dose treatment on early bactericidal activity (EBA) by analysis of time to positivity (TTP) automatically detected in BACTEC MGIT 960 (MGIT) for mycobacterial liquid culture. Adequate microbiological response is defined as sputum culture conversion between day 0 and 15 or difference in TTP between day 0 and 5 by at least 25 hours, day 0 and 8 by 50 hours or day 0 and 15 by 75 hours based on unpublished data of TTP-dynamics observed in our observational cohort study^24^ and the literature.^33–35^

Study participants randomised to the intervention group will be followed for a total of 28 months to record any signs of relapse. Study participants randomised to standard of care will have a follow-up visit 6 to 12 months after completion of treatment and any signs of relapse beyond that point will be retrieved by data collection from the Swedish national TB registry 24 months after treatment completion. In addition to registration of relapse, final treatment outcome is recorded according to WHO definitions.^36^

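### After month 4 relapse is ascertained by different methods in the two arms, and the text conflicts on adverse-event collection for controls in months 5–6

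*Protocol article*

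**What the plan says.** The trial is a "multicentre open-label randomised controlled phase II study" (Study design). Ten controls are treated for 6 months and 30 intervention patients for 4 months (Data analysis plan; Table 2).

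**Relapse.** The section on collection of safety measures and follow-up sets one method per arm. For the experimental arm: "Study participants randomised to the intervention group will be followed for a total of 28 months to record any signs of relapse". Controls have a single visit 6 to 12 months after they finish treatment. For later events, "any signs of relapse beyond that point will be retrieved by data collection from the Swedish national TB registry 24 months after treatment completion". The Figure 1 legend agrees: after four months the intervention arm enters the charted follow-up, "meanwhile the control group is followed up according to routine care (not included in the picture"). The same legend says that relapse is registered in both arms.

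**Adverse events.** The Figure 1 legend confines close safety monitoring to the first four study months and describes the charted activity as the same in both arms. The safety section sets weekly checks in the intensive phase and then says "During the continuation phase the same safety routine is applied every second week", without limiting this by arm or month. The abstract has adverse effects monitored for the whole study. The Data analysis plan makes incidence and severity of adverse events the main secondary outcome and gives no time window.

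**The concern.** When one arm is followed by the study team and the other largely through a registry, a difference in recorded relapses can come from how hard each arm was searched. Knowledge of the allocation adds to this. The Introduction says that earlier attempts to shorten treatment failed through relapse, and the patient involvement section foresees a phase III trial based on these results. Readers will therefore set the two relapse counts beside each other, whether or not a test is planned.

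For adverse events the problem is narrower. Controls are still on rifampicin and isoniazid in months 5 and 6, and two parts of the article describe different data collection for that period. An analysis plan can define a window later, but it cannot recover questionnaires or blood tests that were never collected.

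**Working it through.** **1. Horizon.** Treatment lengths are from Table 2, follow-up from the safety section.
- Intervention: 4 + 24 = 28 months, which reproduces the stated total if it means 24 months after treatment.
- Control: 6 + 24 = 30 months from start.
- Both arms therefore have 24 months after treatment. The 2-month gap appears only when counting from randomisation.

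**2. How much of the control follow-up rests on the registry.** The visit falls at month 6+6=12 to 6+12=18 from start. The registry alone covers the remaining 24−12=12 to 24−6=18 months after treatment. The text describes no registry look-up for the intervention arm.

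**3. Size of differential detection (assumed, not in the documents).** Take equal true risk, full detection in the intervention arm, and detection s in controls. The apparent relapse ratio, intervention to control, is 1/s. Expected detected control relapses are 10 × risk × s, shown here for a true risk of 5%.

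| s | Apparent ratio | Control relapses detected, of 10 | Missed |
|---|---|---|---|
| 1.00 | 1.00 | 0.50 | 0 |
| 0.90 | 1.11 | 0.45 | 0.05 |
| 0.75 | 1.33 | 0.375 | 0.125 |
| 0.50 | 2.00 | 0.25 | 0.25 |

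The intervention arm would show 30 × 0.05 = 1.5.

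**4. Precision.** With zero events the exact 95% upper limit is 1 − 0.025^(1/n): 30.8% for 0/10 and 11.6% for 0/30. One control relapse found or missed moves that arm's rate by 1/10 = 10 percentage points. Fisher's exact test of 5% against 20% has power of about 4%.

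**5. Adverse events in control months 5–6.** Two readings are possible.
- *The Figure 1 legend governs.* Structured collection ends at month 4 in both arms, and controls' last two treatment months have routine care only.
- *The safety section governs.* Controls have two-weekly checks to month 6 and the intervention arm to month 4. Whole-treatment incidence then covers 6 against 4 months.

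Under the second reading, with an assumed constant hazard h and no true difference, cumulative incidence is 1 − exp(−h × months). At h = 5% per month this is 1 − exp(−0.20) = 18.1% over 4 months and 1 − exp(−0.30) = 25.9% over 6. At h = 2% it is 1 − exp(−0.08) = 7.7% and 1 − exp(−0.12) = 11.3%. A constant hazard is a crude assumption, since pyrazinamide and ethambutol stop at week 8 in both arms.

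**The case against.** The best defence is that relapse is not a comparative endpoint here. The Data analysis plan plans no relapse test. Its between-arm items are drug exposure and early bactericidal activity, and the Discussion presents the trial as informing tolerability and PK-PD. At a 5% risk, imperfect detection loses a fraction of one control patient. Any bias would probably run against the new regimen and so be conservative. All of this stands and limits the weight of the point. It does not remove it, because relapse is registered in both arms by methods that the article itself makes different.

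Three stronger readings are tempting and not supported:
- *Follow-up differs in length.* It does not, counted from the end of treatment.
- *Controls who leave Sweden are counted as relapse-free.* The article does not say how emigration is handled. The statement that "the vast majority (85%) of patients are migrants that have acquired their infection prior to arriving to Sweden" concerns where infection was acquired and gives no rate of leaving.
- *Late adverse-event rates will be compared unfairly.* No late comparison is stated, and follow-up after treatment is described only as recording relapse.

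The intervention arm's visit schedule may be in Figure 1, which is not shown. Near-complete detection in that arm is therefore an assumption too.

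On adverse events, one can argue that either text read alone is workable. That is so, but they cannot both govern control months 5–6.

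**Conclusion.** The point holds as a difference in method. After month 4, relapse is sought through study follow-up in one arm. In the other it is sought through routine care, one visit and then the registry, within a matched 24-month post-treatment horizon. The likely direction is against the intervention, but neither direction nor size is established: the ratios of 1.11 to 2.00 follow wholly from assumed detection of 90% to 50%. With 10 controls, chance outweighs this bias. A reader might infer that the trial's relapse result is invalid. What is supported is that the two counts should not be compared as they stand.

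The conflict over adverse-event collection in control months 5–6 is real and touches the main secondary outcome, which has no common window. The primary pyrazinamide exposure outcome and the bactericidal-activity data from days 0 to 15 are unaffected. The point merits a change but does not threaten the trial's main purpose.

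**What to change.** 1. Run the same national TB registry query for both arms, 24 months after treatment completion or at one common time from randomisation, and state which. The first keeps the post-treatment horizon equal. A common query at month 30 gives 30−4=26 months after treatment in the intervention arm and 30−6=24 in controls.
2. Use that query as the common source for any between-arm relapse statement, and report relapses found only by study follow-up separately. Record how each relapse was first detected, since one picked up at a study visit may then also enter the registry. If the query is not extended, report relapse per arm without comparison.
3. Limit the between-arm adverse-event comparison to months 0–4, where study activity is described as identical, and report control months 5–6 descriptively.
4. Reconcile the Figure 1 legend with the safety section on what is collected from controls in months 5–6.

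The cost is one further registry extraction, possibly with a short ethics amendment, and some rewording. Relapses found only by study follow-up drop out of the between-arm contrast but remain reported. No sample-size figure changes.
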